# Effectiveness of deep cervical fascial manipulation and yoga postures on pain, function, and oculomotor control in patients with mechanical neck pain: study protocol of a pragmatic, parallel-group, randomized, controlled trial

**DOI:** 10.1186/s13063-021-05533-w

**Published:** 2021-08-28

**Keywords:** Cervical pain, Musculoskeletal manipulation, Active stretching, Soft tissue therapy, Eye movements, Connective tissue

## Abstract

**Introduction:**

Mechanical neck pain (MNP) is a commonly occurring musculoskeletal condition that is usually managed using electrical modalities, joint mobilization techniques, and therapeutic exercises, but has limited evidence of their efficacy. Pathology (densification) of the deep cervical fascia that occurs due to the increased viscosity of hyaluronic acid (HA) may induce neck pain and associated painful symptoms of the upper quarter region. Fascial manipulation (FM) and yoga poses are considered to reduce the thixotropy of the ground substances of the deep fascia and improve muscle function. The purpose of this study is to investigate the effect of FM and sequential yoga poses (SYP) when compared to the usual care on pain, function, and oculomotor control in MNP.

**Methods:**

This FaCe-Man trial will recruit 160 patients with subacute and chronic mechanical neck pain diagnosed using predefined criteria. Participants will be randomized to either the intervention group or the usual care group, using a random allocation ratio of 1:1. Patients in the intervention group will receive FM (4 sessions in 4 weeks) and SYP (12 weeks) whereas the standard care group will receive cervical mobilization/ thoracic manipulation (4 sessions in 4 weeks) and therapeutic exercises (12 weeks). The primary outcome is the change in the numeric pain rating scale (NPRS). The secondary outcomes include changes in the patient-specific functional scale and oculomotor control, myofascial stiffness, fear-avoidance behavior questionnaire, and elbow extension range of motion during neurodynamics test 1.

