#### Sample size

The sample size is estimated based on the primary outcome NPRS. The threshold for MCID in MNP patients with and without UE symptoms is 2.2 and 1.5, respectively [51], whereas the MCID for NPRS in patients with chronic musculoskeletal pain is 1 [52]. Thus, MCID is considered as one in order to have a substantial sample size in this trial.
$$ n=\kern0.5em \frac{2\ \left({Z}_{1-\alpha /2}+{Z}_{1-\beta}\right).\kern0.5em {\sigma}^2\left[\ 1+\left(m-1\right)\rho \right]}{m{d}^2} $$

*d* - MCID = 1

Z_1-α/2_ = 1.96 at *α*=0.05

Z1-β = 1.28 at 90% power

*m* = Number of time points/follow-ups = 5

*ρ* = Intraclass correlation = 0.4

$$ n=\frac{2\times {\left(1.96+1.28\right)}^2\times 2.{5}^2\times 2.2}{5\times {1}^2}=\mathbf{58} $$

Accounting for dropout rate/non-response rate

*N*^*x*^ = *N*/1 – dropout rate; for 10% dropout rate

Required sample size = **64** participants/group.

Total number of participants in the trial = **128**

To detect a difference of one on the NPRS scale (pain intensity) between the groups assuming a standard deviation of 2.5 at a 5% level of significance and 90% power and 10% dropout, the minimum number of participants required in each group is **64**.

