### Methods: assignment of interventions

#### Allocation

##### Sequence generation

Random assignment of participants to either control or the intervention group will be conducted at an allocation ratio of 1:1. The sequence will be computer-generated using R software, with two strata, which include group 1: age (18–30) and group 2: age (31–45). Sixteen blocks of 10 people (5 in the control group and 5 in the intervention group) will be used.

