#### Statistical methods

For all the continuous primary and secondary outcomes listed in Table 2, where repeated measurements are to be taken, repeated measures ANOVA will be used. The Student’s *t* test will compare the intervention group (IG) and the control group (CG) during interim assessments. The difference in means will be used for the analysis of continuous variables. All statistical tests will be carried out at a 5% (two-sided) significance level. All analyses will be carried out using the R software, which is open-source software. Patients will be stratified into group 1 ages 18–30 and group 2 ages 31–45. Subgroup analysis will be done based on these groups.

**Table 2 Tab2:** Summary of reporting outcome measures

Variables/outcomes	Methods of analysis

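### The protocol gives two unexplained enrolment totals, 160 and 128, and on the inputs listed in its sample-size section 128 gives about 85% power, not 90%

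*Protocol article*

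**What the plan says.** The protocol article gives the size of the trial in three places.

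- Abstract, Methods: "This FaCe-Man trial will recruit 160 patients with subacute and chronic mechanical neck pain".
- Sequence generation: "Sixteen blocks of 10 people (5 in the control group and 5 in the intervention group) will be used", which is 16 × 10 = 160 places.
- Sample size: "Total number of participants in the trial = 128". The closing sentence of that section says "the minimum number of participants required in each group is 64".

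The Sample size section aims at a between-group difference of 1 NPRS point. Its planning values are given as "assuming a standard deviation of 2.5 at a 5% level of significance and 90% power and 10% dropout". It lists 5 time points and an intraclass correlation of 0.4. The Statistical methods section makes the test two-sided: "All statistical tests will be carried out at a 5% (two-sided) significance level".

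The participant totals in the Trial status table belong to an amendment log and are not used here.

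**The concern.** The enrolment total is a basic commitment of a protocol, and the current text makes two. A reader of the eventual report could not tell whether a trial that closed at 128 had completed recruitment or had fallen 20% short (32/160), nor whether one that closed at 160 had overrun.

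The choice also bears on power. The 128 comes from a worked line whose repeated-measures factor disagrees with the inputs printed above it. If those inputs are the intended ones, closing at 128 raises the type II error from the planned 10% to about 15%.

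**Working it through.** **Inputs, all from the Sample size section unless noted.** SD 2.5; difference d = 1; z-values 1.96 and 1.28; m = 5 time points; ρ = 0.4; dropout 10%; two-sided 5% (Statistical methods). The value m = 5 agrees with Table 3, which shows five NPRS assessments after baseline.

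**Formula.** n per group = 2 (1.96 + 1.28)² SD² F / (m d²), with F = 1 + (m − 1)ρ. The symbolic formula in the article omits the square on the z-sum (unsquared, with F = 2.2, it would give 17.8). The worked line squares it, and so do I.

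**Step 1: reproduce the stated figure.** The worked line uses F = 2.2:

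- n = 2 × 10.4976 × 6.25 × 2.2 / 5 = 57.7, so 58.
- 58 / 0.9 = 64.4, which the article takes as 64, giving 128. Rounding up would give 65 and 130.

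So 128 is reproduced only with F = 2.2 and with rounding down.

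**Step 2: use the listed m and ρ.** F = 1 + 4 × 0.4 = 2.6:

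- n = 2 × 10.4976 × 6.25 × 2.6 / 5 = 68.2, so 69 evaluable per group.
- 69 / 0.9 = 76.7, so 77 randomised per group, 154 in total.

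**Step 3: power at each total.** Power = Φ(d / √[2 SD² F / (m n)] − 1.96), with n the evaluable number per group after 10% dropout: 64 × 0.9 = 57.6 and 80 × 0.9 = 72.

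- 128 randomised, F = 2.6: √(32.5 / 288) = 0.336; 1 / 0.336 − 1.96 = 1.017; power 84.5% (84.8% if 57.6 is rounded to 58).
- 160 randomised, F = 2.6: √(32.5 / 360) = 0.300; 1 / 0.300 − 1.96 = 1.368 (unrounded root); power 91.4%.

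**Step 4: other readings of the factor 2.2.**

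| Reading | F | Total required | Power at 128 | Power at 160 |
|---|---|---|---|---|
| m = 5, ρ = 0.4 (as listed) | 2.6 | 154 | 84.5% | 91.4% |
| m = 5, ρ = 0.3 | 2.2 | 130 | 89.9% | 95.1% |
| m = 4, ρ = 0.4 | 2.2 | 164 | 82.5% | 89.9% |

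In the second row, 58 evaluable per group in place of 57.6 gives 90.1%. The third row also yields 2.2 inside the bracket, but the worked line divides by 5, so it does not match that reading as a whole.

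**The case against.** The best defence is that 64 per group is called a minimum, so a required 128 and a planned 160 can coexist. The two operational statements, on recruitment and on the block schedule, agree on 160, and if they are followed power is 91.4% or 95.1%. This has some force, but it does not settle the matter. The same section also gives 128 outright as the number in the trial, and no sentence presents the further 32 as a margin.

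A second defence is that the factor 2.2 may be what was meant and the printed correlation the slip. That stands as a possibility: with ρ = 0.3 there is no material power shortfall at 128. A reader might infer that only 160 can meet the 90% target. The document supports that only on its listed inputs.

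Three further inferences are tempting and should not be drawn.

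- A reader might suspect that recruitment could be closed at 128 after a look at accumulating results. Nothing in the text says so. The Data monitoring committee section plans no formal stopping guidelines or interim analysis. The t tests at interim assessments mentioned under Statistical methods are not tied to any recruitment decision.
- A reader might infer that one age list will run out, because 160 places leave no spare for 160 patients in two strata. The article does not say how the sixteen blocks divide between the strata, so any probability of this rests on an assumed split.
- A reader might count it as an error that 128 is not a multiple of 10. A trial may end within a block.

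**Conclusion.** The conflict between 160 and 128 is real, lies wholly in current text, and holds under every reading of the sample-size inputs.

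The sample size is also misstated on its own listed inputs: they require 154 randomised, not 128. At 128 the power is about 85%, some 5 points below target; at 160 it is about 91%. This part rests on m = 5 and ρ = 0.4, the only values the article prints, together with SD 2.5, a difference of 1 point and 10% dropout. If ρ = 0.3 was intended, both totals reach about 90% or more, and what remains is the disagreement between totals plus the downward rounding of 64.4.

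**What to change.** In the Sample size section, either correct the factor to 2.6 or state the m and ρ that were intended, then recompute and round up. Give the resulting single total in the abstract, the Sample size section and the block schedule.

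On the listed inputs, 160 (80 per group) exceeds the required 154, is already announced and matches the sixteen blocks, so 128 can be replaced by 160. If ρ = 0.3 was intended and 160 is kept, add a sentence giving the reason for recruiting above the requirement.

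Optionally, generate surplus blocks in each age stratum so that neither list can run out.

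The cost is an amendment of wording and, if the option is taken, a longer computer-generated list. On the listed inputs it needs no patients beyond the 160 already announced.

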**Discussion:**

If found effective, FM along with SYP investigated in this trial can be considered as a treatment strategy in the management of mechanical neck pain. Considering the magnitude of the problem, and the pragmatic and patient-centered approach to be followed, it is worth investigating this trial.

**Trial registration:**

ClinicalTrials.gov CTRI/2020/01/022934. Registered on January 24, 2020 with ctri.nic.in. Clinical Trials Registry – India.

**Supplementary Information:**

The online version contains supplementary material available at 10.1186/s13063-021-05533-w.

## Background

Mechanical neck pain (MNP) is a commonly occurring musculoskeletal condition in the adult population [1]. MNP is defined as non-specific pain in the area of the cervicothoracic junction exacerbated by neck movements [2, 3]. The prevalence of MNP ranges from 5.9 to 38.7% [3]. Almost half of the MNP patients may develop chronic symptoms, contributing significantly to global disability and substantial societal burden [1, 3]. A study that investigated the factors associated with neck and shoulder pain in young adults has reported that increased screen-based activities (prolonged use of computers and mobiles) without any physical activity resulted in a higher prevalence of neck pain among adults [4].

MNP may be associated with temporomandibular pain, oculomotor dysfunctions, headaches, non-otogenic otalgia, and non-odontogenic toothache [5]. Because of the multifactorial presentation of painful symptoms, MNP is often termed as non-specific neck pain and is managed conservatively using electrical modalities, joint mobilization techniques, and therapeutic exercises [3].

A systematic review has shown multiple cervical manipulation sessions may provide better pain relief and functional improvement than medications. The authors have also reported that cervical manipulation and mobilisation present similar results for all outcomes, including pain, function, and patient satisfaction [6]. Considering the association between decreased thoracic mobility and cervical pain as well as the higher risk of cervical manipulation complications, thoracic manipulation is preferred [7]. Also, a review has reported the effectiveness of therapeutic exercises in neck pain patients is uncertain without high-quality evidence [8]. Moreover, the clinical prediction rules pertinent to the conventional management of neck pain in adults are at the preliminary stage which mandates the need for their validation [9].

The mechanosensitive neural tissue is considered a primary feature in cervicobrachial pain syndrome with pain in the upper quarter region (UQR) [10, 11]. Nevertheless, Gangavelli et al. reported that only 19.9% of cases are of neurogenic origin [12]. In addition, Butler had proposed that not all “positive tension tests” indicate adverse neurodynamics, and the neurodynamics tests are not specific enough to indicate abnormal neural mobility [13–15]. In patients with positive neurodynamics tests, there can be diverse problems that are not related to “neural tension” that may create a painful response [14]. A systematic review of anatomical studies has reported that deep cervical fascia (DCF) links the muscles of the UQR, thus forming the in-series myofascial continuity, which may induce nociceptive pain in cervicobrachial pain [16, 17].

Studies have shown the existence of myofascial expansions, where the DF connects the different muscles of the UQR [18, 19]. The deep cervical fascia (DCF) at the neck has myofascial continuity proximally and distally, forming a myofascial continuum (MC) of the upper quarter. The DCF and its MC that links the head, neck, and upper extremity are illustrated in Fig. 1 [19, 20]. The presence of nociceptors in such connective tissues may convey nociceptive signals directly. Besides, the proprioceptors may change to nociceptors, thus transforming the mechanical stimuli into pain signals. Studies have reported that changes in the hyaluronan of the connective tissues may alter the viscoelasticity of the myofascia resulting in the activation of nociceptors. Thus, dysfunctions of the DCF may be the causative factor in non-specific pain and other symptoms of the eye, head, neck, and arm associated with MNP [17, 21].

**Fig. 1 Fig1:**
[figure not shown]
Deep Cervical Fascia and its Continuum (© [name] & [name])

Oculomotor dysfunctions associated with MNP are the sensorimotor dysfunctions of the oculomotor system characterized by pursuit, saccade, and convergence deficiencies [22, 23]. EMG studies have revealed an altered activation of the temporomandibular joint and neck muscles in patients with visual defects [23, 24]. Studies have shown an increase in the cervico-ocular reflex (COR) [23] and ocular symptoms such as visual stress, lachrymation in patients with non-specific neck pain attributing it to the impaired receptors at the facets and the deep muscles of the cervical spine [25–27].

The fascia’s inability to extend and accommodate the craniocervical musculature tension is hypothesized to have occurred due to the modification of the DCF in chronic MNP. Restoring the physiological elasticity of the DCF by FM may result in appropriate afferent inputs from the receptors present in the neck muscles that elicit COR, leading to improved oculomotor control.

The increased viscosity of hyaluronan leads to the formation of adhesions and the generation of tensional forces. The adhesions alter the activation of mechanoreceptors, leads to the non-physiologic movement of the joints, resulting in pain and dysfunctions [28–31].

Fascial manipulation (FM) is hypothesized to restore the restricted movement of collagen and elastin fibers within the ground substance. The manipulation of the densified center of coordination (CC) and center of fusion (CF) points might improve the flexibility of the myofascial structures, thereby improving the fascial mobility and the associated symptoms [17, 28, 31]. Besides FM, sequential yoga poses (SYP) also focus on the myofascial lines. It restores fluid flow, decreasing the thixotropy in the ground substances, leading to the muscles’ effective and efficient functioning [32–34].

Patient-reported outcome measures (PROM) such as the numeric pain rating scale (NPRS) and patient-specific functional scale (PSFS) are used in assessing pain and function, respectively [35].

The presentation of various symptoms of the upper quarter with MNP leads to an extensive treatment without any significant treatment effect. Concomitant occurrence of symptoms such as neck pain, headache, and visual dysfunctions may occur due to the impairment in the anatomical fascial connections between the deep cervical fascia (DCF), epicranial fascia, and the tenon’s fascia. A well-designed pragmatic study incorporating manipulation of the DCF, and its continuum in MNP is needed. Thus, the FaCe-Man trial aims to study the efficacy of FM of DCF and SYP when compared to usual care (cervical mobilization (CM), thoracic manipulation (TM), cervicothoracic manipulation (CTM), and home-based therapeutic exercises (TE) on pain, function, and oculomotor control in patients with sub-acute and chronic MNP.

### Objectives

#### Primary research question

Are fascia directed treatment approaches, including 4 sessions of FM in 4 weeks and 3 months of home-based SYP (5 days/week) better than usual care, including 4 sessions of CM, TM, CTM, and 3 months of home-based TE (5 days/week) for improving pain, function, and oculomotor control in patients with subacute and chronic mechanical neck pain?

#### Primary objective

The primary objective of this study is to determine the effectiveness of fascia directed approach that includes FM (4 sessions in 4 weeks) and 3 months of home-based SYP (5 days/week) as compared to 4 sessions of CM, TM, CTM, and 3 months of home-based TE (5 days/week) on pain using numerical pain rating scale (NPRS).

#### Primary research hypothesis

The hypothesis of this study is there will be a significant improvement in MNP patients who undergo fascia-directed treatment approaches (FM and SYP) in reducing pain.

#### Secondary objectives

To study the effectiveness of fascia directed treatment approaches (FM & SYP), in comparison to usual care on function, oculomotor control, elbow extension range of motion (ROM) during ULNT1, viscoelastic properties (tone, stiffness, elasticity) of myofascia, and patient-reported fear avoidance behavior.

#### Trial design

The FaCe-Man trial is a pragmatic, outcome assessor-blinded, randomized, controlled superiority trial with two parallel groups. Randomization will be implemented as stratified (age-based) block randomization with a 1:1 allocation ratio. The trial report is based on the SPIRIT guidelines and checklist-2013 [36] (Additional file 1) and TIDieR guidelines for intervention description and replication [37, 38] (Additional files 2 and 3).

## Methods

### Methods: participants, interventions, and outcomes

#### Study duration

This study period is planned from October 8, 2019, to October 7, 2023.

#### Study setting

Outpatient clinic - Department of Orthopedics at Kasturba Hospitals (recruitment), Center for Sports Science, Medicine, and Research (Interventions and Outcome Measures) and Outpatient Clinic - Department of Speech and Hearing (Outcome Measures), Manipal Academy of Higher Education, Manipal, Karnataka, India.

#### Study flow

The study flow is outlined in Fig. 2.

**Fig. 2 Fig2:**
[figure not shown]
Consort Flow diagram

#### Eligibility criteria

##### Inclusion criteria

Participants: Individuals with sub-acute or chronic MNP for more than 3 weeks.Age group: Between 18 and 45 years.

##### Exclusion criteria

Patients diagnosed with any bony lesions, inflammatory diseases, skin infections, vestibular balance disorders, sensory and motor deficits of the UQR, and the history of surgery/trauma to the UQR in the last year or presenting with conditions that are considered as red flags for manual therapy.

### Interventions

In this study, usual care includes therapeutic exercises, cervical mobilization (CM), and thoracic manipulation (TM). Joint mobilization/manipulation will be provided during day 1 and the next three treatment sessions with a 1-week interval between the sessions. Patients in the intervention group will receive FM and instructions regarding home-based SYP. Instructions regarding the home-based therapeutic exercises for the usual care group and sequential yoga poses for the interventional group will be provided during the first treatment session. Regular monitoring of the exercises and SYP will be done during different treatment and follow-up sessions.

#### Usual care group (CM and TM)

Manipulation involves unidirectional thrust movement, whereas mobilization includes smooth oscillatory movements. Large amplitude oscillatory movements and small amplitude at the end range will be used for treating pain and stiffness, respectively. When treating muscle spasm, the rhythm is mainly a sustained position at a point where further movement is restricted by muscle spasm for 1 min in the order of 10–20 s. This sustained progressive position is interspersed with oscillatory movements [39–45].

Therapeutic exercises:

Home-based exercises will be taught, including upper cervical spine mobility and stretching of neck musculature to improve mobility and flexibility. Following this, re-education of the craniocervical flexion (CCF) and progressive training of deep neck flexors and extensors, as well as axio-scapular muscles, will be taught. The details of the usual care are shown in Additional file 2: TIDieR Control group (Usual care group) [37, 38]. The patient’s home-based exercises are illustrated in Additional file 4: Therapeutic exercises - Information leaflet [3].

#### Intervention group (FM and SYP)

The intervention group will receive fascial manipulation and sequential yoga poses.

##### Fascial manipulation

Fascial manipulation (FM) targets the densified points located on the deep muscular fascia termed as the center of coordination (CC) and the center of fusion (CF), which are located on the ligaments, retinacula, and intermuscular septa [17, 19, 28]. The densification may occur at the CC and CF points and are formed due to repetitive abnormal mechanical stresses such as abnormal neck postures. Palpation and movement verifications of the CCs and CFs of the most dysfunctional MFU will be done before selecting the points to be treated for each treatment session. A study on the reliability of movement and palpation assessments in patients with coxarthrosis using the FM method has demonstrated high reliability even if performed by novice FM practitioners [46]. After the identification of a densified center of coordination (CCs) and center of fusion (CFs) by palpation, FM is done by deep friction massage using elbows or knuckles for 5–8 min at each densified CCs and CFs [45, 47, 48]. FM is considered to stimulate these intrafascial mechanoreceptors (paciniform corpuscles, ruffini endings, and interstitial receptors) resulting in altered regulation of motor units thus changing the tissue metabolism and fluid dynamics [19, 48].

